## **9. Randomisation**

PASTA is a cluster RCT in which the unit of randomisation is an ambulance station or, in the case of large ambulance stations, an identifiable paramedic team within a station. Clusters comprise the paramedics based within teams or at stations. Randomisation will be performed prior to the start of the trial in each region. Within each ambulance service, ambulance stations or paramedic teams (according to local service configuration) which feed into a study hospital will be randomised to delivering the PASTA pathway or to continue with standard stroke care. All paramedics will be given the option of not assisting with the study.

Stations or teams within each service will be stratified according to size (categorised as small, medium or large according to the personnel and resources available), and distance from the nearest study hospital admitting stroke patients (distance categorised as near or far, reflecting the local geography of each ambulance service). The use of these stratifying variables will ensure that PASTA care paramedics (intervention) and standard care paramedics (control) are approximately equally matched by operational characteristics. The actual randomisations will be performed, documented and reported by two statisticians at Swansea University Clinical Trials Unit.

Stations and teams randomised to continuing standard care will be informed that there is an ongoing study of pre-hospital assessment for stroke patients, but not be given any further information about the intervention. For paramedics who are part of a station or team randomised to deliver the PASTA pathway, study specific training and documentation will be provided. Paramedics who opt out of the study or who work within a station or team that was not selected to be involved in the study will continue to deliver standard care.

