## 18. Statistical analysis

Analysis is by 'treatment allocated'; that is, primary and secondary efficacy and safety outcomes analyses will all use the study group allocation of the attending paramedic; only paramedics completing the study specific training will be considered as members of the intervention group. Thus, data will be analysed pragmatically according to paramedic group allocation, irrespective of the care process actually experienced by individual participants.

The primary end point measure is the proportion of participants who received intravenous thrombolysis. The primary analysis will compare the proportion of participants who received thrombolysis in the two arms of the study using logistic regression. Models will include various covariates and factors, including (but not limited to) participant age and gender and admission time and date (used to define a covariate to reflect background trends).

Secondary outcomes, including stroke severity 24 hours after thrombolysis (measured by an NIHSS score), inpatient mortality and dependency (modified Rankin Scale), will be analysed by appropriate ordinal and binary regression models, with appropriate adjustment for potential covariates and factors.

To address the second objective (that is, the impact of the intervention on various time intervals related to the emergency call), we will use appropriate statistical models. For time intervals between events which always happen (for instance, emergency call to hospital admission), we will employ linear models (after appropriate transformation), again adjusting for statistically significant covariates and factors; if the distributions of residuals are markedly non-normal, further transformation or bootstrapping will be considered. Residual diagnostics will also be used to identify outliers; identified outliers will be excluded and the analysis recalculated. For events which may or may not happen (for instance, emergency call to thrombolysis), we will analyse outcomes via binary regression models and survival analysis, comparing intervention and control arms using the framework of accelerated life testing; both approaches will again accommodate statistically significant covariates and factors.

Other clinical objectives will be addressed by appropriate descriptive statistical measures.

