## **Sample size**

Sample size considerations are based on postulated and standardised statistical effects of the intervention on binary outcomes. A change from 0.1 to 0.13 (for instance, in the proportion of cases with a good mRS score at day 90) is equivalent to an effect of 0.1, while a change from 0.43 to 0.53 (for instance, in the proportion of patients receiving thrombolysis) is equivalent to an effect of 0.2.

In the initial protocol for this trial, sample size considerations assumed equal patient numbers per arm, allowed for 3% attrition for a primary outcome collected at day 90, used conventional values of 80% power and 5% significance, and a relatively small change between arms from 0.1 to 0.13 in the proportion of cases with a good mRS score at day 90, equivalent to a standardised statistical effect of 0.1. These considerations led to an initial recruitment target of 3640 (1820 cases per arm).

However, in early 2017, informal review of internal phase data showed that some key assumptions were unlikely to be met in practice. Specifically, overall recruitment was lower than anticipated, while intervention paramedic training completion rates meant a persistent imbalance in patient numbers in the two arms, with typically 8-10 control cases for every 5 intervention cases.

Following discussions with stakeholders (including both trial oversight committees and funders), it was agreed to amend the primary outcome to the proportion of patients receiving intravenous thrombolysis; postulating a change from 0.43 to 0.53 in the proportion of patients receiving thrombolysis, equivalent to a standardised statistical effect of 0.2. Sample size considerations were therefore re-assessed, factoring in attrition of 1%, power of 90% (and 5% significance), and an average cluster (patients per paramedic) of 5 with an intra-cluster correlation coefficient of 0.02. In addition, an imbalance of 2 control cases per intervention cases was incorporated. This gave a revised recruitment target of 1297 study participants (865 control cases versus 432 intervention cases).

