#### *Quantifying uncertainty in estimates of cost effectiveness:*

Bootstrapping will provide estimates of the imprecision surrounding estimates of costs and incremental cost per unit of outcome. Results will be presented as cost effectiveness acceptability curves (CEACS)[32]. Probabilistic sensitivity analyses will be carried out on key cost parameters. If after initial analysis it is found that the cost-effectiveness of the intervention is sensitive to one or more inputs, an Expected Value of Perfect Parameter Information (EVPPi) will be undertaken focusing on those inputs[35].

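### The primary analysis is fixed as logistic regression with no stated method for correlation within the randomised station or team, and the sample size allows for clustering only by paramedic

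*Protocol*

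**What the plan says.** Protocol section 9 defines the design: "the unit of randomisation is an ambulance station or, in the case of large ambulance stations, an identifiable paramedic team within a station". Randomisation is stratified: "Stations or teams within each service will be stratified according to size", and also by near or far "distance from the nearest study hospital admitting stroke patients".

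Protocol section 18 gives the primary method: "The primary analysis will compare the proportion of participants who received thrombolysis in the two arms of the study using logistic regression". On adjustment it adds: "Models will include various covariates and factors, including (but not limited to) participant age and gender and admission time and date". The list of covariates is open. Station, team, ambulance service, size and distance are not named in it, and neither is any way of handling correlation between patients.

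The Sample size part of section 18 does allow for clustering. It assumes "an average cluster (patients per paramedic) of 5 with an intra-cluster correlation coefficient of 0.02" and arrives at 1297 recruited and 1284 analysable participants.

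Section 20 says of the economic results: "Bootstrapping will provide estimates of the imprecision surrounding estimates of costs and incremental cost per unit of outcome". It does not say what unit is resampled.

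**The concern.** In a cluster trial, two patients from the same randomised unit tend to be more alike than two patients from different units. Standard logistic regression treats them as independent and so gives standard errors that are too small. A chance difference between stations could then be reported as an effect of the pathway.

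The protocol accepts that correlation exists, because it enlarges the sample for it. The analysis it names does not carry that through. The only cluster it defines for inference is the paramedic, so an analyst who follows the sample size section could model the paramedic alone and still miss the unit that was randomised.

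Correlation at station level is plausible on the protocol's own account. Section 5 reports large differences between services in thrombolysis rates. Section 8 selects hospitals to differ in service design and past efficiency. Section 9 randomises stations that feed those hospitals. Patients of different paramedics at one station will often reach the same hospital. The stratifiers are size and distance within each service, not hospital, so they need not balance this.

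**Working it through.** **Inputs from protocol section 18:** proportions 0.43 and 0.53 (standardised effect 0.2), two-sided 5%, power 90%, two controls per intervention case, 5 patients per paramedic, intra-cluster correlation (ICC) 0.02, attrition 1%.

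**1. Reproduce the target.** The design effect is DE = 1 + (5 − 1) × 0.02 = 1.08.

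- With the standardised effect, controls = (1.960 + 1.282)² × 3 / 0.2² ≈ 788, so the total is 1.5 × 788 ≈ 1182. Then 1182 × 1.08 ≈ 1277, and 1277 / 0.99 ≈ 1290.
- The two-proportion formula gives 783 controls, 1174.5 in total, 1268 after the design effect and 1281 after attrition. With a continuity correction the last figure is 1330.

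All three lie within 3% of the stated 1297. The target is consistent with a design effect of 1.08 having been applied.

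**2. Error of an analysis that ignores clustering, at the protocol's own figures.** The naive standard error is too small by √DE, so the true type I error is 2 × [1 − Φ(1.96/√DE)].

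- √1.08 = 1.039 and 1.96/1.039 = 1.886, so the true error is about 5.9%.
- The correct confidence interval is about 4% wider than the naive one.

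**3. Allow for correlation between different paramedics of one station or team.** The protocol gives neither the number of patients per station or team (m) nor an ICC at that level (ρ), so both are assumptions. Keeping 0.02 within paramedic:

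DE = 1 + 4 × 0.02 + (m − 5) × ρ

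With ρ = 0 this returns 1.08. With ρ = 0.02 it equals 1 + (m − 1) × 0.02. That is the upper end if 0.02 is right for patients of one paramedic, because it places all the correlation at station level.

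| m (assumed) | ρ (assumed) | DE | True type I error | Correct CI wider by |
|---|---|---|---|---|
| any | 0 | 1.08 | 5.9% | 4% |
| 20 | 0.01 | 1.23 | 7.7% | 11% |
| 20 | 0.02 | 1.38 | 9.5% | 17% |
| 30 | 0.01 | 1.33 | 8.9% | 15% |
| 30 | 0.02 | 1.58 | 11.9% | 26% |
| 50 | 0.01 | 1.53 | 11.3% | 24% |
| 50 | 0.02 | 1.98 | 16.4% | 41% |

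If the ICC were only 0.005 throughout, 10 to 50 patients per station would give about 5.5% to 7.9%.

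**4. Why the unit matters for the sample size.** With 1284 analysable patients, a correctly adjusted analysis has about 90% power at DE 1.08. At ICC 0.02 it has about 82%, 77% and 67% for 20, 30 and 50 patients per station.

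These are large-sample approximations that assume clusters of similar size.

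**The case against.** The strongest reply is that silence is not a decision. A random-intercept logistic model, GEE with a logit link and cluster-robust variance are all forms of logistic regression, and section 18 excludes none of them. A statistical analysis plan may exist, and details of this kind are often left to it. The sample size shows that the planners knew about clustering.

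Part of this stands. The protocol nowhere says that clustering will be ignored, and a reader should not infer that it does. But section 18 does not defer the primary method: it fixes one, and goes into detail on transformation, outliers and accelerated life models. The open wording covers covariates and factors, which are not a correlation structure. Station entered as an ordinary fixed factor would not serve either, because arm as randomised is constant within station or team. And the one cluster that is named is the wrong one.

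Three stronger readings are tempting and are not supported:

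- **That the model holds patient covariates only.** The list is expressly open, so service, size and distance are unnamed, not excluded.
- **That leaving out the stratifiers makes the result too optimistic.** After stratified randomisation, their omission usually makes inference conservative and costs precision. Only unmodelled clustering produces the optimism.
- **That the secondary models and the economic bootstrap share the fault.** Section 18 promises appropriate models for secondary outcomes, and the bootstrap sentence in section 20 names no resampling unit. Both are unspecified, not shown to be wrong.

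**Conclusion.** The point holds. The primary method as stated does not match the randomised unit, and the allowance for clustering in the sample size is tied to a different unit. Run as written, the primary test has a true error of about 5.9% and an interval that should be about 4% wider, on the protocol's own ICC and cluster size. That inflation is modest.

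The larger figures, about 9.5% to 16.4%, require 20 to 50 patients per station or team sharing an ICC of 0.02. The protocol supplies neither value, so a reader should not take them as the trial's actual error rate. They show what is at risk if correlation extends across the paramedics of a station. The matter deserves correction even at the lower figure, because it concerns the validity of the primary test and is cheap to put right.

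**What to change.** Amend protocol section 18 so that the primary logistic model accounts for the randomised station or team. A random intercept at that level, or GEE or cluster-robust standard errors at that level, would each do. Add a small-sample correction if clusters are few. For scale, 1284 patients at 20 to 50 per station would mean about 64 down to 26 stations (1284/20 and 1284/50).

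Add ambulance service, station size and distance as covariates, for precision.

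Reconcile the paramedic-level cluster in the Sample size part with the station or team in section 9: give the expected number of patients per station or team and an ICC at that level, and restate the power.

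Apply the same principle to the secondary models, and state in section 20 that the bootstrap resamples stations or teams.

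The cost is protocol wording, minor analysis work and a somewhat wider confidence interval. It should be settled before any unblinded analysis.

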This study will evaluate the clinical and cost effectiveness of a paramedic-initiated ambulance and hospital care pathway which seeks to facilitate clinical and radiological assessment of patients presenting with acute stroke symptoms in order to specifically reduce delays in the delivery of intravenous thrombolysis. Patient and professional views about the care pathway will also be described. This Paramedic Acute Stroke Treatment Assessment (PASTA) pathway consists of structured pre-hospital information collection, prompted pre-notification, structured handover of information in hospital, assistance with simple tasks during the first 15 minutes of hospital assessment, a checklist to confirm progress after 15 minutes and a paramedic request for feedback before departure. The pathway has been developed through systematic review of the literature regarding enhanced roles of paramedics, and developmental workshops with clinicians and support personnel in order to define professional roles and operational boundaries which are feasible whilst maximizing value for patient care.

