### **6.2 Objectives**

- To determine whether the PASTA pathway improves patient care and outcomes. Primary outcome: proportion of patients receiving intravenous thrombolysis. Secondary outcomes: stroke severity 24 hours after thrombolysis (National Institute of Health Stroke Scale (NIHSS)[21]), complications after thrombolysis, inpatient mortality, discharge destination, discharge dependency (modified Rankin Score (mRS)[22]), assistance at discharge, 90 day dependency (mRS), 90 day destination, assistance at 90 days.
- To describe the impact of the PASTA pathway on time intervals from emergency call and hospital admission to first brain imaging, thrombolysis treatment (if given), ASU admission and formal assessment of swallowing safety.
- To describe the number and subsequent diagnoses of suspected stroke patients who travelled to hospital with a study paramedic but following assessment at hospital were not given a diagnosis of stroke ('stroke mimics').
- To determine the cost-effectiveness of the PASTA pathway relative to standard NHS stroke care.

- To report patient experiences during the PASTA pathway, including confidence in the care process and information received about diagnosis and treatment.
- To report professional views and perspectives (paramedics and hospital staff) of the acceptability and feasibility of the PASTA pathway in the clinical setting.

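### In the linear models of time intervals, residual outliers are dropped without being limited to recording errors, so real long delays can be removed and standard errors understated

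*Protocol*

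**What the plan says.** Section 18 of the protocol divides the time intervals of the second objective into two groups.

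- **Linear models.** The first group is introduced as "For time intervals between events which always happen (for instance, emergency call to hospital admission"). Here "we will employ linear models (after appropriate transformation), again adjusting for statistically significant covariates and factors". If residuals are markedly non-normal, further transformation or bootstrapping is to be considered. Then comes the rule at issue: "Residual diagnostics will also be used to identify outliers; identified outliers will be excluded and the analysis recalculated".
- **Binary and survival models.** The second group is introduced as "For events which may or may not happen (for instance, emergency call to thrombolysis"). No outlier exclusion is written for it. On covariates, "both approaches will again accommodate statistically significant covariates and factors".

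The rule gives no cut-off, does not ask whether an outlying value is a recording error, and does not say whether the full-data fit or the refit is the main result. The sensitivity analyses named in Section 18 do not include a comparison with and without outliers, although the list is left open.

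The objective served is in Section 6.2: "To describe the impact of the PASTA pathway on time intervals from emergency call and hospital admission to first brain imaging", and on to thrombolysis, stroke unit admission and swallow assessment. Section 5 gives the purpose of the pathway: "in order to specifically reduce delays in the delivery of intravenous thrombolysis".

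**The concern.** A large positive residual in a model of a time interval is usually a patient who waited a long time. Unless the time was recorded wrongly, that wait is part of the outcome, and in this trial it is the kind of outcome the pathway is meant to make rarer. Deleting such patients selects on the outcome after randomisation. It also sits badly with the commitment at the start of Section 18 to analyse patients by the attending paramedic's allocation whatever care they received.

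Two things are at stake.

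- **The estimate.** If the benefit lies partly in fewer long delays, exclusion removes part of it.
- **The standard error.** The refit computes its residual variance from data whose tails have been cut, but the estimate itself does not become correspondingly more precise. The interval is too narrow and the test rejects too often.

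Because the cut-off is open, it could also be chosen after the residuals have been seen.

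**Working it through.** **Inputs from the protocol.** 856 control and 428 intervention analysable outcomes, and two-sided 5% tests with 95% confidence intervals (Section 18). The protocol gives no figure of its own for the interval analyses, so there is none to reproduce.

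**Assumptions, because the protocol gives no value.** Cut-offs of 2, 2.5, 3 and 4 residual SD; one deletion and one refit; a two-group linear model on the log scale; independent patients.

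**Step 1: standard error and type I error with no effect and normal residuals.** For cut-off c, let φ be the normal density, P the share of data kept, a = 2cφ(c), and V = P − a the second moment of the retained data. In large samples

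- reported SE after the refit ÷ full-data SE = √V / P
- true SD of the refitted estimate ÷ its reported SE = √(1 + 2a + a²/V) = k
- actual type I error = 2 × [1 − Φ(1.96/k)]

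| c | a | P | V | √V/P | k | type I, formula | type I, simulation |
|---|---|---|---|---|---|---|---|
| 2 | 0.2160 | 0.9545 | 0.7385 | 0.900 | 1.223 | 10.9% | about 10.5% |
| 2.5 | 0.0876 | 0.9876 | 0.8999 | 0.961 | 1.088 | 7.2% | about 7.0% |
| 3 | 0.0266 | 0.9973 | 0.9707 | 0.988 | 1.027 | 5.6% | about 5.6% |
| 4 | 0.0011 | 0.9999 | 0.9989 | 1.000 | 1.001 | 5.0% | about 5% |

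Example for c = 2: 1 + 2(0.2160) + 0.2160²/0.7385 = 1.495, so k = 1.223, and 2 × [1 − Φ(1.96/1.223)] = 10.9%. Formula and simulation agree within simulation error.

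**Step 2: other residual shapes, still with no effect.** With heavy-tailed (t, 4 df) or right-skewed (gamma, shape 4) residuals, simulated type I error was 8.1% to 9.2% at 2 SD, 6.4% to 6.8% at 2.5 SD and 6.4% to 6.5% at 3 SD. With gamma residuals, practically all excluded cases were long times. With symmetric residuals, half were.

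**Step 3: an effect through long delays only.** Assume a residual SD of 0.4 on the log scale, and sixfold delays in 8% of control and 4% of intervention patients. The true effect is −(0.08 − 0.04) × ln 6 = −0.04 × 1.792 = −0.072.

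| Analysis | Mean estimate | Coverage of the 95% interval |
|---|---|---|
| all data | −0.072 | 96% |
| cut-off 3 SD | about −0.048 | about 85% |
| cut-off 2.5 SD | about −0.026 | about 59% |
| cut-off 2 SD | about −0.011 | about 31% to 33% |

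At 4 SD the estimate is almost unchanged, because the delays inflate the fitted SD. The pooled within-arm delay variance is 1.792² × [(2/3)(0.08 × 0.92) + (1/3)(0.04 × 0.96)] = 3.21 × 0.0619 = 0.199, so the fitted SD is √(0.16 + 0.199) = 0.60. A typical delayed control patient then has a residual of (1.792 − 0.08 × 1.792)/0.60 = 2.7 SD.

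**Step 4: would median or robust regression protect the effect?** In the same scenario the difference in medians averages about −0.020 and Huber regression about −0.029. Both lose more than deletion at 3 SD, because they also down-weight long delays.

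**Step 5: covariates chosen by significance.** With eight candidate covariates balanced between arms, keeping only those with p < 0.05 gives type I error of 4.4% to 5.8%, and a true SD 1.00 to 1.02 times the reported SE. Only an assumed imbalance of 0.2 SD in every covariate raises it, to 6.6% to 8.8%.

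**The case against.** The best defence has four parts.

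- **Scope.** Exclusion is written only for the linear models, and the one example given there is call to hospital admission. Call to thrombolysis, the delay named in Section 5, goes to binary and survival models without exclusion. This stands. A reader might infer that the rule removes the thrombolysis delays the pathway targets, and the text does not support that. Times to scan, stroke unit and swallow assessment plausibly fall in the linear group, but the protocol does not assign them.
- **Size.** Everything depends on a cut-off that the analysis plan may fix. This stands in part: at 3 SD with normal residuals the inflation is small, and at 4 SD there is none to speak of. But a cut-off would not supply what the rule lacks, namely a limit to recording errors and a full-data main result.
- **Mechanism.** The scenario in Step 3 is severe. The pathway prompts pre-alert and structured handover for every patient, which suggests a general shift in times rather than fewer extreme ones. This stands; Step 3 shows what can happen, not what is expected.
- **Mitigation.** The plan transforms first, may bootstrap, and a recalculation implies that a full-data fit exists. This is true. That the refit would be the reported result is an inference. Still, the exclusion is worded as something that will be done, whereas bootstrapping is only to be considered.

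A reader might also infer from "again adjusting for statistically significant covariates and factors" that choosing covariates by significance itself makes the standard errors too small. Step 5 does not bear this out without an imbalance between arms that the documents do not state.

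**Conclusion.** The point holds for the linear interval models only. As written, the rule drops patients on the basis of their outcome, can remove real long delays, and understates the standard error. Type I error rises from 5% to about 5.6%, 7.0% and 10.5% at 3, 2.5 and 2 SD with normal residuals, and is about 5% at 4 SD. In the assumed scenario where the effect acts only through fewer sixfold delays, about a third of it is lost at 3 SD (−0.048 against −0.072) and about 85% at 2 SD (−0.011 against −0.072).

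These sizes rest on assumed cut-offs, residual shapes and delay rates. The direction of the standard-error fault does not depend on the delay scenario. The loss of effect does, and a pathway that shortened all times alike would lose much less.

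The second objective is descriptive and these outcomes are secondary. The primary comparison of thrombolysis proportions and the target of 1297 are untouched. The point should be corrected, but it does not threaten the trial's main conclusion.

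**What to change.** Replace the outlier sentence in Section 18 with wording to this effect:

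- All times verified against source stay in the main analysis. Only confirmed recording errors are corrected, by someone who does not know the arm.
- Non-normal residuals are handled by transformation, with bootstrap or sandwich standard errors for the mean difference on the chosen scale. The plan already allows transformation and bootstrapping. Resampling should be by cluster, as the trial is cluster randomised.
- Outlier exclusion, with its cut-off fixed in advance, is reported only as a labelled sensitivity analysis beside the main result.

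Median or M-estimator regression should not be the main remedy, since it discounts the same long delays. Regression on an upper quantile may be added to describe them directly.

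As a minor point, the interval models should include the stratification factors of Section 9 (station size and distance from hospital) and a covariate set named in advance, whether or not they prove significant. Distance bears directly on travel time. The reason is pre-specification, not a demonstrated error in the standard errors.

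The cost is wording only. The main interval may be somewhat wider than after exclusion, and checking extreme times against source takes a little site effort.
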